### Sample size

A power analysis was conducted to determine the sample size required for this study, using the ‘FactorialPowerPlan’ function within the R-package ‘MOST’.^34^ The study is designed as a factorial experiment with 3 factors and 64 clusters (eight conditions with four groups per condition per country). To detect a small effect with an 80% power and alpha of 0.10 (as recommended for factorial trials in MOST),^35^ considering a small amount of intraclass correlation (ICC) in the absence of intervention (ie, ICC=0.01) and low clustering of change scores (ICC of change scores=0.10), the sample size should include approximately 7 families per cluster, corresponding to 448 families. To consider drop-out after recruitment, it is estimated to recruit approximately 10–12 families per cluster (640–768 families).

### Randomisation and blinding

The randomisation will be carried out at the University of Klagenfurt. A randomisation website (https://www.randomizer.org) will be used to generate random numbers for allocating clusters to different conditions. Randomisation will be stratified by country, with four clusters from each country assigned to one of the eight experimental conditions. The randomisation list will be shared with the research manager at ALTERNATIVA and HYA. This information will be shared via email from [name] (University of Klagenfurt) to the researcher managers at ALTERNATIVA and HYA only. They will keep this information concealed from all participants until after baseline assessments.

At the baseline assessment, both participants and data assessors will be unaware of the group assignments. After the baseline data collection is finished, the research managers at each site will notify the participating families of their group allocation. Data assessors responsible for the assessments will also be blinded to the allocation throughout the study including at postassessment to minimise bias. However, after baseline assessments, participants cannot remain blind due to their involvement in the programme implementation. To maintain the integrity of the study, contamination will be rigorously monitored.

### Data collection and outcomes

Outcomes will be assessed at baseline and postassessment, approximately, 8 weeks later. Data collection from adolescents and caregivers will be conducted primarily using computer-assisted self-report questionnaires on tablets (open-source software platform, Open Data Kit), with data assessors assisting adolescents and caregivers in completing the questionnaires. Adolescents and caregivers will complete assessments separately. Data assessors will receive comprehensive training from the study investigators. This training will cover ethics, informed consent procedures, safety procedures, adverse event reporting and interviewing techniques.

Outcome measures without official translations were adapted and translated following best practice guidelines for cross-cultural adaptation (Piolanti *et al*; Waller and Mueller *et al*).

#### Primary outcomes

The study will assess four primary outcomes: adolescent emotional problems (internalising), adolescent social support, family functioning and attendance (for both adolescents and caregivers). Adolescent internalising problems will be assessed using the parent-report version of the child behaviour checklist (CBCL) for ages 6–18.^36^ Adolescent social support will be measured using the adolescent-report Kidscreen-52, peers and social support subscale^37^ and the medical outcome study social support survey, emotional support subscale.^38^ Family functioning will be assessed using the family assessment device, general family functioning subscale, as reported by caregivers.^39^ Attendance will be measured with the percentage of group PLH sessions attended by caregivers and adolescents.

#### Secondary outcomes

Secondary outcomes encompass additional endpoints expected to show changes as a result of the PLH programme and add-on components. These include adolescent- and caregiver-reported measures of family communication and functioning, parenting practices, loneliness, social support, well-being, behavioural and emotional problems, psychological distress, parental stress, socioemotional skills and health-economic measures. The full list of questionnaires for these and subsequent outcomes is provided in the supplementary material (online supplemental table S1 and S2, appendix 3). Concerning the health-economic evaluation, tools will include standardised measures of health-related quality of life, such as the EQ-5D-5L for caregivers and EQ-5D-Y-3L for adolescents.^40^ In addition, the economic evaluation will incorporate two specific tools: the Oxford CAPabilities questionnaire—Mental Health^41^ completed by caregivers, which provides a multidimensional capability well-being assessment, and version 2 of the PECUNIA resource use measurement instrument,^42^ for caregivers and a proxy version for adolescents, which provides a detailed assessment of broader resource use and will be costed using internationally validated unit costing methods.^43^

#### Other prespecified outcomes

Other prespecified outcomes include measures related to participant characteristics, costs as well as implementation and staff outcomes that may influence the programme’s effectiveness. These outcomes include adolescent body mass index, assessed for descriptive purposes using self-reported and caregiver-reported height and weight; caregiver alcohol use; adolescent-defined problems, where adolescents identify and rate the severity of their top concerns; and post-traumatic stress in both adolescents and caregivers (online supplemental table S2, appendix 3).

Direct implementation cost data will be collected from multiple sources. A purposefully designed cost questionnaire will capture the comprehensive personnel time associated with the training and delivery of the intervention, while additional organisational, material, transportation and consumable costs will be gathered from finance records.

Implementation and staff outcomes include the collection of enrolment rates, weekly attendance records by facilitators and fidelity assessments of PLH sessions conducted by programme supervisors. The implementation of the HAT component and the adolescent peer components will be assessed using a short questionnaire filled out by the facilitators. PLH sessions in both countries will be recorded for supervisory purposes, with one session being assessed using the PLH-FAT.^30^ Additionally, facilitators and supervisors will complete questionnaires on well-being and, for those who are caregivers, parental stress.

#### Process evaluation

Postintervention focus groups will be organised with a subset of adolescents, caregivers and intervention staff. Each focus group will consist of six to eight participants, with a minimum of four groups conducted in each country (adolescents, parents, facilitators and supervisors). The purpose of these focus groups is to collect information for further programme adaptations and to address process evaluation questions regarding the context, implementation and mechanisms of change of the programme. We will also seek to capture feedback on various programme component combinations by including participants who experienced all programme components (all on/high condition).

### Statistical analysis

Analyses will examine the main effect of each component and interaction effects using regression analyses, with adjustments based on baseline data. For pre- and postassessments, intent-to-treat analyses accounting for clustering and stratification by country will be used. Separate models will be tested using effect coding for treatment effects.^44^

Indirect models based on the hypothesised theory of change will be examined using a Mplus software^45^ or R^46^ and accounting for clustering within groups and using bootstrapping procedures (eg, engagement booster component increasing attendance, which, in turn, is related to greater changes in primary and secondary outcomes). Multigroup analyses or t-tests at baseline will be performed to identify differences between countries and other contextual or demographic variables. Any missing data will be assessed and managed using either multiple imputation or full information maximum likelihood estimation, following the intention-to-treat analysis protocol.^47^

#### Health-economics analysis

To comprehensively evaluate the value of the eight experimental combinations, we will employ a cost-consequences analysis (CCA).^48^ The CCA examines the cost and outcomes for each experimental combination, detailing the cost of resources used and the (health) outcomes achieved (eg, changes in CBCL internalising scores^36^ and EQ-5D-Y scores).^40^ This information allows for a clear comparison of the relative value of each combination by presenting both cost and outcome impacts alongside each other systematically and provides the basis for the planned optimisation strategy using a multicriteria decision analysis (MCDA) framework.^49^

#### Process evaluation and staff outcomes analysis

Descriptive statistics will be employed to summarise data concerning attendance, fidelity and characteristics of facilitators. Additionally, the study will explore differences in attendance linked to the baseline characteristics of participants (eg, gender) and characteristics of the intervention’s delivery (eg, study location), as well as changes in staff well-being based on the questionnaires administered before and after the intervention.

### Qualitative analysis

Transcripts from the focus groups will be analysed using thematic and framework analysis,^50^ drawing on both inductive and deductive approaches to generate codes.

### Selection of the optimised intervention: decision process

The criteria for optimisation in this study are designed to identify and include the most beneficial and good value for money, scalable combination for the upcoming RCT in Phase 3 of FLOURISH. To achieve this, we will implement a systematic selection process. We will first assess the effect of each component level (ie, different levels of administration vs non-administration) on study outcomes. Next, we will examine two-way and three-way interactions between the components. The various component combinations will be compared based on the incremental increases in overall benefit and overall cost within an MCDA. Those options that are dominated will be eliminated. For the remaining options, we will use cost–benefit optimisation to select the final combination for Phase 3.

### Patient and public involvement

Advisory groups were set up and consulted on the existing services and challenges, and intervention design and scaling-up considerations in each country, informing the design of the programme tested in Phase 1. The groups include adolescents, caregivers, intervention staff and professional experts (six to eight participants and four groups in each country). The advisory groups are planned to be consulted for further feedback during the project. Any feedback would be summarised in notes, organised into a matrix by key themes and stakeholder type and analysed using thematic content analysis.

### Participant timeline

The study implementation timeline varies between North Macedonia and Moldova to accommodate practical considerations unique to each context. Figure S1 in the online supplemental material, appendix 3 shows the study flowchart. Recruitment of potential caregivers and adolescents will begin after cluster randomisation and is scheduled for October 2024 in North Macedonia and December 2024 in Moldova. Recruitment will continue until the target sample size of 320 enrolled families per country is achieved. In North Macedonia, the intervention and related assessments will be conducted in two waves (beginning in October 2024 and January 2025), while one wave will be used in Moldova (beginning in January 2025). Specific dates may be subject to change to accommodate any practical deviations that arise during the study implementation. These timing variations will be considered in the analyses. Randomisation will ensure that each phase receives all eight conditions, maintaining balance.

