### Participants and recruitment

The study will involve primary caregivers and their adolescents aged 10–14 years. For inclusion in the study, caregivers will have to meet the following criteria: they must be at least 18 years old at the baseline assessment, live with the adolescent in a household where the adolescent has slept at least four nights per week in the previous month, be able to speak at least one of the local languages (Romanian or Macedonian) and provide consent for both their own and their adolescent’s participation in the study by signing an informed consent. Adolescents must be between 10 and 14 years old at the baseline assessment, and both the caregiver and the teen must agree to participate in the study. In North Macedonia, adolescents aged≥14 are also required to provide consent in order to comply with local legal and ethical requirements. An example of the informed consent for caregivers and adolescents is included as a supplementary document (online supplemental appendix 2). Exclusion criteria for both caregivers and adolescents include significant psychiatric disorders, acute distress or physical health conditions that could impede their ability to participate in the study. These are assessed through an exclusionary statement as a part of the consent procedures.

All interested families meeting the criteria above will be eligible to participate in the study, with additional efforts made to include more economically and socially vulnerable groups using a proportionate universalism approach. This method focuses on individuals at higher than average risk without the need for preliminary screening.^29^ In North Macedonia, the recruitment process will primarily take place in schools, whereas in Moldova, it will be conducted in youth clinics. Families will be invited via multiple means to join the study (eg, school referrals, clinic referrals and community outreach) and provided an informational document that explains the study’s objectives, intervention specifics, the voluntary nature of involvement, data handling procedures, potential risks and benefits and provides contact details for additional questions or clarifications.

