The programme will be implemented by the current staff and established networks of ALTERNATIVA and HYA. This staff includes data assessors, facilitators and supervisors. Data assessors are trained research staff responsible for administering participant assessments, ensuring the accurate data collection. Facilitators are trained professionals with prior experience in parenting interventions, responsible for delivering the intervention, leading sessions and guiding participants through skill-building activities. Supervisors are experienced senior staff who provide oversight and support to facilitators, ensure programme fidelity and conduct facilitator performance evaluations. Facilitators, supervisors and data assessors must be 18 years or older, participate in training, agree to fulfil their respective roles in programme delivery, supervision or assessment and provide consent.

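### Clusters are randomised before families are recruited and local research managers hold the list, but concealment is not stated for those who recruit families or place them in groups

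*Protocol article*

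**What the plan says.** **Order of events.** Under Participant timeline: "Recruitment of potential caregivers and adolescents will begin after cluster randomisation".

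**Who holds the list.** Under Randomisation and blinding, the University of Klagenfurt generates the allocation, and "The randomisation list will be shared with the research manager at ALTERNATIVA and HYA". The same paragraph limits the email to those managers. Their duty is then given: "They will keep this information concealed from all participants until after baseline assessments".

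**Who is blind.** "At the baseline assessment, both participants and data assessors will be unaware of the group assignments". Later, "After the baseline data collection is finished, the research managers at each site will notify the participating families of their group allocation". For outcome measurement, "Data assessors responsible for the assessments will also be blinded to the allocation throughout the study including at postassessment to minimise bias".

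**Who delivers and how families arrive.** Under Participants and recruitment: "The programme will be implemented by the current staff and established networks of ALTERNATIVA and HYA". Recruitment is mainly through schools in North Macedonia and youth clinics in Moldova, by several routes (referral and community outreach among them), with extra effort to reach vulnerable families and no screening step.

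**What a cluster is.** Sample size counts 64 clusters as four groups per condition per country. The core programme section describes delivery to groups of 10–12 adolescent–caregiver pairs.

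**The concern.** In a cluster trial that recruits after randomisation, individual families are not randomised. The comparison is protected only if the people who decide which family joins which cluster do not know the cluster's condition. Here the conditions are attached first and the families come afterwards, while at least one person in each implementing network knows the allocation before baseline is complete.

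If someone with that knowledge influences who is approached, or which group a family joins, the two levels of a component could hold different kinds of family. For example, keener families might be steered to groups with vouchers, or higher-need families to groups with the adolescent workshops. Attendance is a primary outcome and plausibly depends on motivation. The main effects and interactions also decide which package goes to Phase 3 (Selection of the optimised intervention), so a distorted contrast would carry into the next trial.

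The Statistical analysis section adjusts for baseline data. That helps with what is measured, but may leave differences in motivation or circumstances that are not.

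**Working it through.** The article gives no figure for this point, so the main check is of the text. A numerical illustration follows.

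**1. Are the groups filled when they are randomised?** Participant timeline puts recruitment after cluster randomisation. Nothing in the article describes clusters as existing units with fixed membership; they are programme groups of 10–12 pairs. The natural reading is that labelled groups are filled later.

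**2. When do the managers have the list?** No release date is given. A duty to conceal the list until after baseline makes sense only if they hold it before baseline ends. The text does not exclude their holding it during recruitment.

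**3. Who is stated to be blind?**

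| Role | Before and at baseline | After baseline |
|---|---|---|
| Families | Blind (stated) | Told their allocation |
| Data assessors | Blind (stated) | Blind, including at postassessment (stated) |
| Research managers | Hold the list | Notify families |
| Those who recruit families | Not stated | – |
| Those who place families in groups | Not stated | – |

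The article does not say who fills the last two roles, or that the research managers do not.

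**4. What would a given amount of bias do?** Inputs from Sample size: 64 clusters, alpha 0.10, ICC of change scores 0.10, and 7 families per cluster (64 × 7 = 448) or 10 (64 × 10 = 640). The size of the bias, *b*, in SD of the change score, is an assumption; the documents give none.

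- Design effect = 1 + (m − 1) × ICC. For m = 7: 1 + 6 × 0.10 = 1.6. For m = 10: 1 + 9 × 0.10 = 1.9.
- Standard error of a main effect (half the families at each level) = 2 × √(design effect / N). For 448: 2 × √(1.6/448) = 0.120 SD. For 640: 2 × √(1.9/640) = 0.109 SD.
- Noncentrality = *b* / SE. For *b* = 0.10: 0.10/0.1195 = 0.84 and 0.10/0.1090 = 0.92.
- Chance of a significant result with no true effect, two-sided alpha 0.10, noncentral t with 64 − 8 = 56 degrees of freedom:

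| Assumed shift *b* | 448 families | 640 families |
|---|---|---|
| 0 | 10% | 10% |
| 0.05 SD | 13% | 13% |
| 0.10 SD | 21% | 24% |
| 0.15 SD | 34% | 39% |

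A shift of 0.10 SD would arise, for example, if 10% of the places at one level of a component went to families differing by 1 SD in prognosis (0.10 × 1 = 0.10). A larger sample makes a fixed bias more likely to reach significance, because the standard error falls and the bias does not.

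**The case against.** The strongest reply is that the plan already closes most of the route. The list goes by email to the research managers and to no one else. On the text, facilitators, supervisors, schools, clinics and assessors do not receive it. The managers are given no recruiting or placing role. Families join and complete baseline without knowing their condition, which removes self-selection by families. Assessors are blind at both time points. Every condition receives the core programme, so no group is left untreated. Who enrols and places families may also be set out in a fuller protocol or a supplement that is not shown.

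Much of this stands, and it rules out several stronger readings that a reader might infer:

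- *That recruitment is unconcealed altogether.* It is not; concealment from families and assessors is explicit.
- *That those who hold the list also recruit.* This is not stated.
- *That the North Macedonian manager holds the January 2025 wave's allocations from October 2024.* The article does not say whether the list is released whole or by wave.
- *That motivation has no baseline measure.* The full questionnaire list is in a supplement that is not shown.
- *That the component contrasts are biased.* Nothing shows this.

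What remains is narrower. The article fixes an order (randomise, then recruit) and a local list-holder before baseline is complete, and it names the groups protected by concealment. Those who recruit and place families are not among them. Restricting the email to the managers protects the allocation only if the managers stay out of recruitment and placement and do not pass the information on. The article states neither condition.

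**Conclusion.** The point holds as a gap in allocation concealment. With recruitment after cluster randomisation and the list held inside the implementing networks, recruitment or placement bias in the component contrasts cannot be excluded. It is a possibility left open by stated procedures, not a demonstrated bias, and baseline adjustment may not fully correct it.

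The conclusion rests on two readings of the text: that clusters are programme groups filled after randomisation, and that the managers hold the list before baseline ends. If clusters turned out to be units with fixed membership, placement across groups would matter less, but knowledge of the condition while inviting families would still matter.

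No size can be derived from the documents. The rise in the false-positive rate from 10% to about 21% (448 families) or 24% (640 families) depends wholly on an assumed 0.10 SD shift. It shows only that a modest imbalance would matter for a decision made at alpha 0.10.

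**What to change.** **Main change.** Under Randomisation and blinding, state that the University of Klagenfurt keeps the list. It releases each cluster's condition to the local research manager only after that cluster's families are enrolled, placed in the group and assessed at baseline. Release would come just before the notification of families that the plan already foresees. That is the latest workable moment: families are told their allocation once baseline is finished, and the vouchers can motivate attendance only if they are announced early. The week 2 peer-support workshop should therefore not be taken as the deadline.

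**If the list must be held locally earlier.** State that list-holders take no part in recruiting or placing families, and that those who do are blind to the list. Extend the concealment sentence from participants to everyone who recruits or places families.

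**For clusters already enrolled.** Report enrolment and baseline characteristics by condition and state the limitation. Enrolment rates are already collected (Other prespecified outcomes), so this adds little work.

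**Cost.** No extra staff and no change to sample size or analysis. The drawback is shorter notice for scheduling the component workshops, because local teams learn each group's condition only when its baseline is complete.
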